### 2.3. Intervention

#### 2.3.1. Procedure

All participants will undergo a total of four visits, including the initial inclusion visit and three experimental visits (T0, T1 and T2), as detailed in Table 1. During the selection visit, qualified personnel will make sure that the young women fulfil the inclusion criteria and that they (or their parent/legal representative in case the girl was a minor) sign the informed consent form after explaining the project itself and after responding to all of their questions. One week after the initial visit, the T0 experimental visit will be conducted to measure all of the baseline assessments before the start of the intervention. At the halfway mark of the program (i.e., three months in), a mid-term measurement will be carried out, denoted as T1. The T2 experimental visit will be scheduled at the end of the program (i.e., after six months of intervention). The three experimental sessions will be identical.

#### 2.3.2. Intervention Group

In order to promote behavior change, we implemented 12 BCTs within the intervention program. Table 2 displays how the BCTs have been implemented within the WISE intervention group.

The WISE intervention is composed of four main features:Exercise videos: participants in the intervention group will receive two HIIT video sessions a week via the WISE app (Figure 2A). These sessions will be carried out at their own home without the need of sport equipment. The exercise program will be developed by two experts in physical activity and sports sciences. Each session will consist of four exercises, and, from session 10, with two different intensities so that the participants can choose one according to their physical condition. The exercises will be different every week. The second session will always have a greater intensity than the first, and the intensity will be increased from week to week. Each session will last between 20 and 30 min and will follow the following structure: 5–7 min of warm-up; 10–15 min of HIIT training; 5–7 min of stretching. Table 3 shows the progression for the WISE exercise protocol. The complete WISE exercise protocol with links to the videos of the sessions can be seen in Table S1.

2.Education in healthy habits: once a week, the participants will receive reading material, with an approximate duration of 2 to 5 min, on general advice on nutrition, sleep (Figure 2B) and well-being (Figure 2C), written by experts in the field. Dietary guidelines will also be created by a team of professionals specialized in nutrition to stimulate the participants and give them basic indications on proper eating behavior. These reading materials will be delivered to the participants through the WISE application and will appear by means of a push notification. The complete list of messages for the WISE participants can be seen in Table S2.3.Activity tracker: participants will be able to check their activity at any time of the day through the Xiao Mi Band 5 smartwatch (Figure 2D). The data will also be displayed in the app with weekly charts so participants can see their progression. The participants will also be able to track their weight and their sleep over time (Figure 2E) through the application. Moreover, their heart rate will be recorded. This tool aims to give feedback on behavior and promote self-monitoring of physical activity.4.Motivational activities: in order to motivate the participants to perform the videos, social media, email, WhatsApp groups and/or other channels, such as Viber (depending on the availability/popularity in each country), will be created for the participants to communicate with each other. In addition, social meetings will be organized through “Open Days” held in each country and transmitted through streaming so all the participants can attend the event. During the “Open Days”, talks on nutrition and physical activity will be held, as well as in-person meetings to perform the exercises. Moreover, the participants can expose their doubts and concerns, which can be solved in a personal manner during these events.

#### 2.3.3. Control Condition

The participants in the control group will benefit from general physical activity recommendations (at the start of the intervention: general physical activity guidelines) and will also have access to the activity monitoring tool supplied by the smartwatch. The content of both groups is summarized in Table 4.

#### 2.3.4. Adverse Events

Throughout the experiment, adverse events will be monitored for each procedure. Any adverse events or reactions that are thought to be causally associated with the intervention will be recorded and managed.

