#### 2.2.2. Recruitment

A total of 300 participants (150 per group) will be recruited between the three countries. Each country will recruit 100 young women for the study. Dissemination of the project will be conducted via email and posters in close contact with universities, schools and local authorities. Through the information of the posters and emails, interested participants will contact the investigators and will be informed about the study in order to decide if they finally want to participate. Those willing to participate will be summoned for a personal interview to check if they meet the inclusion criteria. Participants who meet the inclusion criteria will be invited to participate in the study and will sign a written consent form before being included in the study. At the start of the study, a wearable device (Xiaomi Mi Band 5) will be distributed to all participants.

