#### 2.2.4. Randomization, Allocation and Blinding

After the first experimental visit (T0), the participants will be randomized using a computer-generated randomization list into one of the two conditions with a 1:1 allocation. The allocation will be transmitted using numbered (0 = control/1 = Intervention), opaque and sealed envelopes, which will be given to the young women and then registered by the data collectors. The assessors will be blinded to the treatment allocation, although double blinding is not applicable in interventions of this nature as it is impossible to conceal the allocation from the participants. The participants will be instructed not to reveal their allocation to the assessors to ensure unbiased assessment.

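### The stated adverse-event recording rule depends on attribution to the intervention, so it does not secure equal recording of harms in the two arms

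*Protocol article*

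**What the plan says.** Section 2.3.4 of the protocol article has two sentences on harms. The first is general: "Throughout the experiment, adverse events will be monitored for each procedure". It names no arm and sets no causality condition. The second says what is done with events: "Any adverse events or reactions that are thought to be causally associated with the intervention will be recorded and managed". No other sentence in the article commits to recording adverse events. Section 2.4.2 and Table 5 list no safety outcome, and Table 1 has no adverse-event row.

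The arms differ in exposure. For the HIIT sessions of the intervention group, section 2.3.2 states: "These sessions will be carried out at their own home without the need of sport equipment". For the comparator, section 2.3.3 states: "The participants in the control group will benefit from general physical activity recommendations", and adds access to the smartwatch monitoring tool. Table 4 gives controls the videos after the programme has ended.

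On blinding, section 2.2.4 says that assessors do not know the allocation, but that "it is impossible to conceal the allocation from the participants".

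**The concern.** Monitoring and recording are different commitments. If an event enters the record when someone attributes it to the intervention, entry depends on a judgement that is itself related to the arm. A sprain in a woman doing impact sessions at home has an obvious candidate cause. The same sprain in a woman who received general guidance and a watch does not.

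Two things are at stake. First, the randomised control group is the natural means of separating injuries due to HIIT from the background rate in women aged 15 to 24, and that use is weakened if background events are captured less completely in one arm. Second, an event judged unrelated in error may leave no record that could be re-examined. The question is a practical one here: participants are sedentary, some are minors, they exercise at home, and section 2.3.2 has intensity rising from week to week. The article's introduction itself links gradual, individualised programming to the prevention of injury.

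**Working it through.** The plan states no adverse-event figure, so there is none to reproduce. The check sets the statements side by side and then writes out what the rule implies.

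**Step 1. Does the monitoring sentence already secure recording?** It promises monitoring. The next sentence defines what is recorded and attaches a condition. If every monitored event were to be recorded, the condition would have no work to do. The two sentences fit together poorly, and a site following the text could reasonably apply the condition.

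**Step 2. Is the condition equally easy to meet in both arms?** In the intervention arm, an event can be attributed to 50 HIIT sessions (Table 4), to the watch and app, or to the study tests. In the control arm, it can be attributed to general guidance, to the watch, or to the study tests. The study tests are common to both arms (plank test, six-minute walk test and conditioned pain modulation in Table 1). The HIIT sessions are not, and they are the most plausible source of attributed injuries.

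**Step 3. What does this do to the recorded contrast?** Let *r* be the true probability that a participant has an event, and *q* the probability that an event is attributed and so recorded, with subscript 1 for intervention and 0 for control. Section 2.2.2 gives the group sizes: "A total of 300 participants (150 per group) will be recruited between the three countries".

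- Expected recorded events: 150 × *r*₁ × *q*₁ and 150 × *r*₀ × *q*₀.
- Recorded risk ratio: (*r*₁ / *r*₀) × (*q*₁ / *q*₀).
- Recorded difference in counts: 150 × (*r*₁*q*₁ − *r*₀*q*₀), against a true difference of 150 × (*r*₁ − *r*₀).

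The recorded ratio equals the true ratio when *q*₁ = *q*₀. By step 2, *q*₁ is expected to exceed *q*₀, so the ratio is inflated by the factor *q*₁ / *q*₀. The difference in counts may be distorted either way: events lost from the intervention arm pull it down, and events lost from the control arm push it up. The article gives neither *r* nor *q*, so no number can be attached.

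**Step 4. Who judges attribution?** The article does not say. Participants know their arm and assessors do not. Deciding whether the programme caused an event generally requires knowing whether the woman was doing it. That judgement therefore either relies on allocation being known or is made without the most relevant fact. Recording first and judging cause separately keeps this difficulty out of the count.

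**The case against.** The strongest reply is that the text does not restrict recording as firmly as a quick reading suggests. A reader might infer that nothing else is recorded, that the control count must be zero, and that the trial can therefore support no safety conclusion at all. The article does not support any of these.

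- The monitoring sentence applies to the whole trial without limit to one arm, and the second sentence does not say that other events are left out.
- The article also uses the word intervention for the trial period as a whole. Section 2.2.1 uses it that way for all candidates' willingness to wear the watch, section 2.3.3 uses it to date the guidance given to controls, and Table 1 lists the control group under its interventions heading.
- Controls undergo the same tests at the same visits, so a control-arm event could be attributed to a study procedure and recorded.
- No safety objective is stated, and attributed events in the intervention arm would still be informative as description.

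A further reply is that this is a condensed article. Forms, timing and relatedness scales are commonly left to the full protocol, and their absence here is no fault.

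These replies stand against the stronger reading. They do not remove the narrower point. The article does not merely leave the recording rule out; it states one, and that rule turns on attribution. Even if the intervention is read to cover both arms, attributing an injury to guidance or a watch is far less likely than attributing it to an impact session.

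**Conclusion.** The concern holds in a limited form. As written, the rule does not assure equal ascertainment of adverse events in the two arms. Recorded counts would not give an unbiased between-arm comparison of harms, and an event wrongly judged unrelated may be lost to later review.

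This rests on two assumptions: that sites apply the recording sentence as it reads, and that attribution is more likely where HIIT sessions are being done. The likely direction is an inflated recorded risk ratio for intervention against control; the size is unknown. The primary outcome, sample size, power and significance level are untouched. If the full protocol already records every event in both arms, the defect is one of wording in the article. If it does not, the change should be made before follow-up data are collected, because unrecorded control-arm events cannot be recovered reliably afterwards.

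**What to change.** Reconcile the two sentences of section 2.3.4. State that:

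- all adverse events are recorded in both arms, whatever their suspected cause;
- all participants are asked about them in the same way at the existing T1 and T2 visits;
- relatedness is entered afterwards as a separate field;
- events are tabulated by randomised arm.

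The cost is one question at two visits that every participant already attends, and a small amount of extra data entry. No new online form is needed for controls, and none should be added for this purpose. The one online form the article describes is the weekly exercise diary (section 2.4.2), and Table 2 lists a weekly diary among the behaviour change techniques of the intervention group, so giving controls something like it could carry part of the intervention into the control arm.

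The change does not remove all asymmetry. Participants know their arm and may report differently. It does remove attribution as a condition for entering the record.

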### 2.4. Outcome Measures

#### 2.4.1. Primary Outcomes

The primary outcome of this study will be the change in daily steps from baseline to three months and six months. Daily steps will be assessed using the Xiaomi Mi Band 5 smartwatch, a reliable wearable activity tracker that has been validated in previous research [35,36,37]. Days with missing data, defined as days with fewer than 1000 steps, based on previous literature [38,39], will be excluded from the analysis [40,41] to ensure accurate and comprehensive data representation.

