## Abstract

Background: Physical inactivity is a serious public health problem for people of all ages and is currently the fourth highest global risk factor for mortality. The transition period from adolescence to adulthood coincides with a marked reduction in participation in physical activity, with more than 50% (and up to 80%) of young adults stopping physical activity. This decrease in physical activity is more evident in women than in men. Despite efforts, existing programs face challenges in effectively initiating and maintaining physical activity among individuals, particularly women, for extended durations. To address these limitations, the Women’s Involvement in Steady Exercise (WISE) randomized controlled trial (RCT) seeks to assess the efficacy of a digital high-intensity training intervention complemented by nutritional plans and other health-related advice. Methods: The study will be a three-center, randomized (1:1), controlled, parallel-group trial with a six-month intervention period. A total of 300 participants will be recruited at three study sites in Spain, Serbia and Italy. The participants will be randomized to one of the two groups and will follow a six-month program. The primary outcome of the study is the daily step count. Self-reported physical activity, the adherence to the exercise program, body composition, physical activity enjoyment, quality of sleep and physical capacities will also be evaluated.

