### Study Aims

The primary goal of the Women’s Involvement in Steady Exercise (WISE) randomized controlled trial (RCT) is to evaluate the adherence to a six-month HIIT program, accompanied by nutritional plans and other health-related advice, delivered via a mobile application, among sedentary young women aged 15 to 24 years. This trial aims to determine the effectiveness of the exercise intervention by assessing the changes in the participants’ daily step count over the six-month period. The secondary objectives include analyzing the medium- and long-term effects of the program on various variables, including physical activity, anthropometric measurements, body composition, physical capacities, well-being and psychological mediators.

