#### 2.4.2. Secondary Outcomes

The secondary outcomes include changes in: (1) physical activity; (2) anthropometric measurements and body composition; (3) physical capacities; (4) well-being. In addition, psychological mediators will also be examined.

The following criteria will be used in order to measure the WISE program adherence [42]:Retention (completion): the participants following the WISE exercise videos and showing up to the follow-up measurements.Attendance: percentage of videos completed of the total of 50 videosDuration: adherence to a minimum of 20 min of exercise two times a week.Intensity: intensity levels of the sessions will be assessed at the end of each session using the modified Borg Scale, which measures perceived exertion [43].

These items will be measured through a weekly online exercise diary, where the participants will be asked if they completed both video sessions. They will also be asked about their perceived exertion after each session. This will allow us to assess whether they are following the 20 min of exercise two times a week rule, completing the video sessions, so we can see the number of videos completed at the end of the program.

Table 1 presents the assessment schedule, following the Standard Protocol Items: Recommendations for Interventional Trials (SPIRIT) schedule template. Table 5 provides an overview of all the outcome measures.

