## 3. Statistical Analyses Plan

All the statistical analysis will be performed using the SPSS version 24 Software (SPSS Inc., Chicago, IL, USA). If adherence issues occur, all analyses will be evaluated by intention-to-treat principles, with a level of significance of 0.05. Continuous outcomes will be presented using mean and standard deviation if they follow a normal distribution. On the other hand, count outcomes, such as WISE sessions completed, will be reported through the median and percentage of achievement. At the basal assessment, an independent-samples Student’s *t*-test will be performed to rule out differences between groups of age and height of participants.

In order to answer the first aim of this study, the changes in the adherence variables, such as daily steps, the Borg scale and the IPA questionnaire, will be analyzed by 1-within-subject factor multivariate analysis of variance (MANOVA). The Bonferroni adjustment will be used for post-hoc comparisons between the T0, T1 and T2 times assessments. On the other hand, the secondary outcomes of the study will be tested by 2-factor mixed MANOVA to analyze the effects of a within-subject factor (time assessment from T0 to T4), the between-subject factor (group) and their interaction. As mentioned above, Bonferroni adjustment will be used for times and groups comparisons. In addition, the same statistical test will be carried out considering the country of origin of the data as a covariate, and the findings will be reported according to their statistical significance. For all the statistical analyses, differences will be declared statistically significant if the *p*-value is less than 0.05. The exact *p*-value and 95% confidence interval will be reported.

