BCTs, behaviour change techniques; WISE, Women’s Involvement in Steady Exercise; RCT, randomized controlled trial.

**Table 3 healthcare-11-01279-t003:** WISE exercise protocol progression.

Month	Session	Work Time	Recovery Time	Level
1	1	20”	20”	Initiation and no impact
	2			Medium-advanced with impact
2	1	20”	15”	Initiation and no impact
	2			Medium-advanced with impact
3	1	20”	10”	Initiation and no impact
	2			Medium-advanced with impact
From week 12th, we introduce 2 different intensity levels in each session (one without impact or less demanding) so the participants can choice between the 2 levels in order to better adapt their effort				
4	1	30”	20”	Medium
	2			Advanced
5 and 6	1	40”	15”	Medium
	2			Advanced

**Table 4 healthcare-11-01279-t004:** Summary of the groups’ content.

Intervention Group (Videos)	Control Group
50 HIIT video exercise sessions	Physical activity recommendations (at the start of the intervention: general physical activity guidelines) *
Communication group	--
Activity monitoring tool (mobile app + Xiaomi Mi Band 5)	Activity monitoring tool (Xiaomi Mi Band 5)
Education in healthy habits	--

HIIT, High Intensity Interval Training. * At the end of the program, the participants will have access to the HIIT video sessions.

**Table 5 healthcare-11-01279-t005:** Outcomes measures of the WISE RCT.

Outcome	Assessment Method
Primary outcome	
Daily step count over 6 months	The Xiaomi Mi Band 5 smartwatch will be used to assess the daily step count. Days with missing data and/or days with fewer than 1000 steps will be excluded from the analysis.
Secondary outcomes	
Physical activity	
Self-reported physical activity and sedentary behaviors	Self-reported behaviors will be gathered using the International Physical Activity Questionnaire (IPAQ). The IPAQ assesses walking and activities of a moderate and vigorous intensity that are performed continuously for at least 10 min in all domains of everyday life (i.e., leisure, occupational, household and transport) in the last 7 days. The IPAQ demonstrates acceptable levels of test-retest reliability and fair to moderate associations with accelerometer measures [40,41].
Anthropometric data and body composition	

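### Daily steps is the primary outcome throughout, but the protocol does not fix it as one quantity, one time point and one between-group test

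*Protocol article*

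**What the plan says.** The Protocol article describes the primary outcome or its analysis in these places:

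- **Abstract:** "The primary outcome of the study is the daily step count", with no time point or summary measure.
- **Study Aims:** the primary goal "is to evaluate the adherence to a six-month HIIT program". The next sentence judges effectiveness by changes in the "daily step count over the six-month period".
- **Section 2.2.3:** the sample size rests on daily step count, with the individual day as the statistical unit.
- **Section 2.4.1:** "The primary outcome of this study will be the change in daily steps from baseline to three months and six months".
- **Table 5:** the primary outcome is "Daily step count over 6 months".
- **Section 2.4.2, under secondary outcomes:** "The following criteria will be used in order to measure the WISE program adherence". The criteria are retention, attendance, duration and intensity.
- **Section 3, first aim:** the quantities analysed are "the changes in the adherence variables, such as daily steps, the Borg scale and the IPA questionnaire". The method named is a MANOVA whose only factor is time within subject. Bonferroni is applied to the post-hoc comparisons among T0, T1 and T2. A group factor appears only in the following sentence, which concerns the secondary outcomes. The significance threshold is 0.05 for all analyses.

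**The concern.** A confirmatory trial needs its primary hypothesis fixed before results are seen: which variable, which summary, which time point, which comparison. Here only the variable is fixed. Change to month 3, change to month 6 and a count over the whole period are different quantities and can give different answers. With no decision rule, the version to emphasise can be chosen after the data are known.

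Two further consequences follow.

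- The analysis attached to the first aim has no group factor. A change over time alone does not use the randomisation. In women selected for low activity and given a tracker, steps could change without any effect of the programme.
- Steps are labelled an adherence variable. A step count does not record whether home video sessions were completed, so a result on steps could be misreported as a result on programme adherence.

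**Working it through.** **1. Which parts of the primary test are fixed**

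| Element | What the text gives | Fixed? |
|---|---|---|
| Variable | Daily steps wherever a primary outcome is named | Yes |
| Summary | No summary (Abstract); individual days (2.2.3); change from baseline (2.4.1); count over the period (Table 5) | No |
| Time point | Months 3 and 6, with no either/both rule (2.4.1); the whole period (Table 5) | No |
| Comparison | One within-subject factor, no group factor (section 3) | No between-group test |
| Outcomes analysed with it | Borg and IPAQ, in an open list (section 3) | No |

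**2. Whether steps, Borg and IPAQ can share one primary analysis**

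IPAQ is a secondary outcome in Table 5. Borg is recorded at the end of each video session (2.4.2). Controls get the videos only after the programme ends (Table 4 footnote), so they have no session scores during the trial, and nobody has one at T0. A joint multivariate analysis that includes Borg could not be a comparison of the randomised groups. The same holds for adherence as defined in 2.4.2, apart from attendance at follow-up visits, which both groups can show.

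**3. What the Bonferroni rule covers**

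Three visits give three pairs: T0–T1, T0–T2 and T1–T2. Each is tested at 0.05/3 = 0.0167, so the error over the three time comparisons is at most 5%. The 3- and 6-month changes from baseline are two of these pairs. As written for the first aim, they are comparisons between times, not between groups.

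**4. Error rate if two between-group tests were run unadjusted**

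The protocol gives no familywise figure to reproduce. Inputs:

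- two-sided alpha 0.05 (2.2.3 and section 3), critical value c = 1.96;
- two tests (months 3 and 6, from 2.4.1);
- correlation r between the test statistics, which is assumed because the document gives none.

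Formula: familywise error = 1 − P(|Z₁| ≤ c and |Z₂| ≤ c), with Z₁ and Z₂ bivariate normal.

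| r | Familywise error |
|---|---|
| 0 | 1 − 0.95² = 9.75% |
| 0.3 | 9.5% |
| 0.5 | 9.1% |
| 0.7 | 8.3% |
| 0.8 | 7.8% |
| 0.9 | 7.0% |

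A third unadjusted version, such as a 6-month summary, would give 12.5% with all correlations at 0.5 and 9.8% at 0.8 (simulation).

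**5. Whether the planned size can carry a clear rule**

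Inputs from 2.2.3: d = 0.50, 240 women (120 per arm) after dropout. Power = Φ(d√(n/2) − z), with d√(n/2) = 0.5 × √60 = 3.873.

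- One test at 0.05: Φ(3.873 − 1.960) = 97.2%.
- Two time points at 0.025 each: Φ(3.873 − 2.241) = 94.9% per test. For 90% power, n per arm = 2 × [(2.241 + 1.282)/0.5]² = 99.3, so 100 per arm and 200 in total.
- Both time points required, each at 0.05: at least 1 − 2 × (1 − 0.972) = 94.4%, if d = 0.50 holds at both.

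The standard two-group formula with the stated inputs gives 85 per arm (170 in total), not 240. That is a separate matter on which this point does not depend.

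**The case against.** The strongest reply is that the primary outcome is never really in doubt. Every place that names it names daily steps. Adherence is called a goal, the next sentence of the aims turns to step count, and adherence itself sits under secondary outcomes. This stands. A reader might infer that adherence is a rival primary endpoint on which success could be claimed, but no passage says so. What remains is a mismatch between the aim and the outcome.

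Second, the article does adjust for multiple time points, and 2.4.1 does not say that either one suffices. This also stands. A reader might infer that each version may be tested at an unadjusted 0.05 and that 9.1% is the trial's error rate. Section 3 does not describe that procedure, and the figure holds only under the stated conditions. The reply does not go further, because the adjustment for the first aim is between times. The wording that extends Bonferroni to groups as well as times follows the secondary-outcome analysis.

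Third, the Table 5 entry is a short label that could mean the same repeated measure as 2.4.1, and an article may leave the exact step summary to a fuller document. This is fair: the label does not define a 6-month average. It does not explain two time points without a rule, or a primary analysis stated without a group factor. Those are in the text as written, not left out of it.

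A reader might also take the mention of long-term effects in the aims as part of this problem. That wording concerns the secondary objectives and has no bearing on the primary endpoint.

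**Conclusion.** The point holds in this form: the primary variable is consistent, but its summary, its deciding time point and its randomised test are not fixed, and the aims and section 3 describe steps as a measure of adherence. This follows from setting the passages side by side and rests on no assumption.

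The error inflation is conditional. It is about 7% to 9.75%, against a nominal 5%, if months 3 and 6 are each tested between groups without adjustment, either suffices, and the correlation lies between 0.9 and 0. Where the stated Bonferroni rule applies, the error is at most 5%. The matter should be settled before group results are seen, because the trial's main conclusion depends on this definition.

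**What to change.** 1. **Name one primary endpoint.** For example, the between-group difference in change in mean daily steps from baseline to month 6, with month 3 and the 6-month summary as secondary. Keeping both time points is also valid if the rule is explicit: both required at 0.05, or alpha split at 0.025 each.
2. **Section 3:** state the between-group test for that endpoint on its own, apart from Borg and IPAQ, and stop calling steps an adherence variable. Without this change, rewording the outcome alone would still leave no randomised primary test.
3. **Section 2.4.1 and Table 5:** use identical wording for the endpoint, and make the statistical unit in 2.2.3 agree with it.
4. **Study Aims:** state the primary aim as the effect on daily steps. Make adherence to the exercise programme a descriptive secondary objective in the intervention arm.

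The cost is protocol and registry wording before unblinding, and month 3 loses its primary status under the single-endpoint option. At the stated d = 0.50 and 240 evaluable women, each of the three options keeps power above 90%, so none needs more participants.
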